## 3. Discussion

This will be the first randomized clinical trial testing the efficacy of neuroscience therapeutic education as a standalone treatment for CM patients. While such treatments hold significant potential, their development faces several challenges, such as creating an appropriate sham. Instead of a traditional sham group, we opted to design a custom control group, delivering migraine-related information in a structured format. This approach aims to create a control group that is both plausible and distinct from the active group, which is critical since patients need to remain unaware of their treatment allocation over the 2.5-month duration. However, to avoid diluting the effect of the active treatment, we ensured the control arm content did not overlap with the educational material in the active arm. Therefore, in CON-A, we chose to provide science-based information about migraine, covering aspects like epidemiology, pathophysiology, and basic clinical knowledge, with a relatively high technical detail level. The content was based on a popular migraine educational book [56]. However, to maintain the distinction, we intentionally excluded content that could influence the patients’ understanding of pain or improve their coping strategies. The goal was to keep the education on “what migraine pain is” (in the control group) separate from “what migraine pain means” (in the active group).

Adherence is another critical consideration. Given the duration of the treatment, with several lessons over an extended period, there is a potential risk of high dropout rates. However, our protocol has been designed to make attendance manageable, with only one lesson per week. Eight out of ten lessons can be attended remotely through a conference platform and last about an hour. In three instances, patients are required to admit to the hospital: at T1 to perform baseline assessment and receive the first lesson in presence, midway thought the TNE treatment to collect the second neurophysiology assessment, and at the end for the recap lesson which has the scope of performing a recap of the prior lessons and reinforce the learning. Although attendance is required, it is not as frequent as other protocols, such as neuromodulation treatments, which typically require visits two to three times a week for one to two months. Patients who decide to discontinue the study will be referred to alternative treatments and will be classified as non-responders in the analysis. Regarding the follow-up duration, while some migraine education studies have followed patients for 12 months [57], we opted for a shorter follow-up period, as in other trials [58], in order to grant a good preventive prediction of neurophysiological tests. Longer follow-ups could be influenced by spontaneous fluctuations that may alter the headache profile [59]. In conclusion, despite the complexities of the TNE protocol, the study incorporates strategies to minimize dropouts. The increasing use of TNE in challenging settings, such as for breast cancer patients [60], demonstrates the high feasibility of these approaches.

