## Abstract

Chronic migraine (CM) is a highly disabling condition, affecting about 2% of the global population. Non-pharmacological treatments can be optimal for their non-invasive nature. This prospective, randomized, double-blind, controlled trial aimed to test the efficacy of therapeutic neuroscience education (TNE) in CM. Early response biomarkers were also evaluated. A total of 80 CM patients were consecutively enrolled and randomly allocated to TNE or a general education program. Treatment effectiveness was evaluated at baseline (T1) and 2 months after the end of treatment (T4). We collected the responses to disability and comorbidity questionnaires at the start (T1) and end of treatment (T3, 10 weeks after start). Early response biomarkers were evaluated at screening (T0) and mid-way through the process (T2, 5 weeks after start). We expected that TNE would provide a greater benefit than the general education program, which served as the primary outcome of this study. We also expected that a change in clinical and neurophysiological measures could potentially occur, reflecting plasticity-induced reorganization and predicting clinical response. This is the first study selectively exploring the effect of TNE as a standalone treatment for CM. A new, effective treatment regime without interactions with other medication could be of great interest as an addition to migraine therapeutic strategies.

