## 2. Materials and Methods

### 2.1. Study Cohort

Consecutive CM patients will be recruited for the study. Eligibility criteria will include a CM diagnosis (with or without MOH) based on the International Classification of Headache Disorders (ICHD-3) criteria [32] and age > 18 years, as recent data suggest TNE is effective in older adults as well [33]. Patients will be enrolled consecutively. Exclusion criteria will include an ICHD-3 diagnosis of another primary or secondary headache disorder (except for MOH), neurological or psychiatric conditions that could affect compliance or neurophysiological assessments (e.g., neurodegenerative disorders, multiple sclerosis, epilepsy, schizophrenia, severe anxiety/depression with HADS >15), chronic pain conditions (e.g., low-back pain, chronic pelvic pain), severe comorbidities related to migraine or systemic diseases requiring concurrent medical treatment, and malignancy. Patients on migraine preventive therapy will be included if their prophylaxis has remained unchanged and ineffective for at least three months prior to recruitment. This treatment will not be down-tapered or discontinued at the study’s onset. Relevant demographic data will also be collected.

Migraine burden will be assessed throughout the study using a headache diary (tracking headache days, pain intensity, and acute medication use) and several validated questionnaires, including the Migraine Disability Assessment (MIDAS), the Headache Impact Test (HIT-6), the Central Sensitization Inventory (CSI), the Pain Catastrophizing Scale (PCS), and the Hospital Anxiety and Depression Scale (HADS) [34,35,36,37,38].

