### 2.3. Randomization, Schedule, and Adherence

Patients will be randomly assigned at a 1:1 ratio using a pre-generated randomization list created in SPSS by an experimenter who will not be involved in patient recruitment, treatment, or data analysis. Participants will be required to attend a full course of 10 lessons, with the first and last sessions conducted in person and the remaining eight delivered remotely via PowerPoint presentations. Lessons will be held in small groups, with the real and control education groups scheduled on different days to prevent interaction between participants from different study arms. The treatment will be considered valid if patients attend at least 8 out of 10 lessons. In case of absence, the PowerPoint presentation from the missed session will be sent to the participant. Additionally, a brief Q&A session will be conducted before the next lesson to review the content and address any questions.

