### 2.10. Plans for Analysis

An a priori calculation of the sample size was performed based on the primary endpoint. In line with studies on CM with MOH, we aim for a between group difference of 3.0 monthly headache days at T4 and a standard deviation of 4.5 [55]. Using an alpha error of 5%, a power of 80%, and a medium effect size, the calculated sample size is 70 patients. Considering a reasonable dropout rate, we plan to recruit 80 patients.

To assess the treatment’s effects on clinical and instrumental outcomes, a generalized linear mixed model for repeated measures (*p*-value < 0.05) will be performed on the primary outcome and, in a sub-analysis, on secondary outcomes. The model will include group and time as fixed effects, time by group as an interaction term, and the outcome as the dependent variable. Covariates will be selected from those identified as significantly different between groups [10]. A correlation analysis will also be conducted between migraine disability indexes and clinical/neurophysiological measures to identify potential biomarkers. False discovery rate correction will be applied to reduce type-I errors.

The number of adverse events (AEs) during the treatment period will be counted separately for the TNE-A and CON-A groups and classified according to common terminology criteria for adverse events (CTCAEs). An AE is defined as any adverse medical event associated with the use of a treatment in humans, regardless of whether it is considered related to the treatment. Causality (relationship to study treatment), action taken, and outcome will be summarized separately.

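### The trial is labelled a test of TNE as a standalone treatment, but it enrols patients who stay on preventive drugs at entry, so it estimates TNE given alone or on top of prophylaxis

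*Protocol article*

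**What the plan says.** Two framing sentences in the protocol article use the standalone label. The Abstract says "This is the first study selectively exploring the effect of TNE as a standalone treatment for CM", and its next sentence speaks of an "effective treatment regime without interactions with other medication". The Discussion opens by calling the trial the first randomised one "testing the efficacy of neuroscience therapeutic education as a standalone treatment for CM patients".

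Section 2.1 (Study Cohort) sets the eligibility rule: "Patients on migraine preventive therapy will be included if their prophylaxis has remained unchanged and ineffective for at least three months prior to recruitment". It continues: "This treatment will not be down-tapered or discontinued", with the sentence ending at the start of the study. The article does not address later changes.

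The formal objective (end of the Introduction) and section 2.2 (Outcome Measures) ask whether TNE works as a preventive treatment compared with general education. Neither says standalone.

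On allocation, section 2.3 says "Patients will be randomly assigned at a 1:1 ratio using a pre-generated randomization list created in SPSS" and mentions no stratification. On analysis, section 2.10 says "The model will include group and time as fixed effects, time by group as an interaction term". Any further covariates are those found to differ significantly between the arms.

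**The concern.** A patient who enters on a preventive drug and keeps it receives TNE in addition to that drug, and has by definition not benefited from the drug. A patient on no preventive receives TNE alone. Both kinds of patient are enrolled, and the primary contrast averages over them. A positive result would therefore show that TNE is better than general education in this mixed population. It would not show that TNE works on its own.

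What is at stake is the claim a reader takes away. The standalone label, next to a remark about other medication, invites the inference that TNE was tested without background preventive drugs. The eligibility rule does not support that inference.

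The covariate rule is a related, smaller matter. Prophylaxis is a plausible prognostic factor and is known at screening. Under the stated rule it enters the model only if chance makes the arms differ significantly.

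**Working it through.** **1. The plan's own figure.** Inputs from section 2.10: difference 3.0 monthly headache days, SD 4.5, alpha 5% (two-sided assumed, as sidedness is not stated), power 80%.

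n per arm = 2 × (1.96 + 0.842)² × 4.5² / 3.0² = 35.3, rounded up to 36, so 72 in total. The stated total is 70, which agrees within two patients. With 70 evaluable patients, t-test power is 78.5%. The sample size is not the problem here.

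**2. What the contrast estimates.** Let s be the share on prophylaxis. The article does not give s, so 25%, 50% and 75% are assumed.

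Average effect = (1 − s) × effect alone + s × effect as add-on.

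Take 3.0 days as the effect alone, vary the add-on effect, and hold the SD at 4.5 with 70 evaluable patients:

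| Assumed add-on effect | s = 25% | s = 50% | s = 75% |
|---|---|---|---|
| 1.5 days | 2.63 days, power 67% | 2.25 days, power 54% | 1.88 days, power 41% |
| 3.0 days | 3.00 days, power 78.5% | 3.00 days, power 78.5% | 3.00 days, power 78.5% |
| 4.0 days | 3.25 days, power 85% | 3.50 days, power 89% | 3.75 days, power 93% |

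The average can lie below, at or above the effect of TNE alone. The documents give no evidence on which row applies.

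**3. How much information bears on TNE alone.** With 70 evaluable patients, about 52, 35 or 18 are off prophylaxis at s = 25%, 50% or 75%. Assuming they split equally between arms, the approximate 95% CI half-width is 1.96 × 4.5 × √(4/n):

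- n = 52: 2.4 days
- n = 35: 3.0 days
- n = 18: 4.2 days

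At a share of one half or more, the half-width is about as large as the 3.0-day target or larger. An estimate in patients off prophylaxis could therefore only be exploratory.

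**4. How the covariate rule behaves.** Take unstratified 40:40 allocation. The chance that prophylaxis use differs by at least 10 percentage points between arms is about 44% at s = 25% and 50% at s = 50%. At s = 50%, a 10-point gap is 22 against 18 patients:

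z = 0.10 / √(0.5 × 0.5 × 2/40) = 0.10 / 0.112 = 0.89.

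A 20-point gap (24 against 16) gives z = 0.20 / 0.112 = 1.79. Neither reaches 1.96, so the rule would leave prophylaxis out in both cases.

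**The case against.** The strongest reply is that the trial's question is not misstated where it counts. The Introduction and section 2.2 ask about TNE against general education, and the design answers that. The label sits only in two novelty sentences, and no hypothesis, endpoint or test depends on it. This stands, and it limits the point to what may be claimed from the result.

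A second reply is that standalone may mean TNE not bundled with another non-drug therapy. The remark about medication interactions fits co-use too, since interactions matter chiefly to people who take other drugs, and the same sentence presents TNE as an addition to existing strategies. That reading is possible, but the article does not define the word. If it is the intended meaning, one clause would settle it.

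A third reply is that the prophylaxis is stable, ineffective and open to both arms. This protects the comparison. It does not make TNE a sole treatment, and patients whose drug has failed need not respond as patients on no drug do.

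A reader might infer three stronger things, and none is supported:

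- **That the comparison is biased.** It is not: patients on prophylaxis are randomised like the rest.
- **That the plan is at fault for giving no estimate by prophylaxis status.** The article is condensed, and such detail may sit in a full protocol or SAP that is not shown.
- **That the trial is underpowered for its standalone question.** The 80% was claimed for the whole trial, never for patients off prophylaxis, and any subgroup figure rests on an assumed share.

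**Conclusion.** The point holds as a mismatch between label and design. The Abstract and Discussion describe a standalone test, while the Study Cohort section enrols patients whose preventive drugs are not withdrawn at entry. The randomised contrast is valid for the stated objective and estimates the effect of TNE against general education, given alone or on top of existing prophylaxis.

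The mismatch follows from the text and needs no calculation. Its numerical effect is unknown. It is nil if TNE works equally with and without prophylaxis. Otherwise it depends on the unstated share and on an assumed difference in effect, so the figures above are illustrations and do not measure a loss in this trial.

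The stated covariate rule is a second, modest weakness. It ties adjustment for a factor known at screening to a chance test between randomised arms. Adjusting for prophylaxis would not turn the overall estimate into a standalone effect.

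**What to change.** 1. Reconcile the Abstract, section 2.1 and the Discussion. Either replace standalone with wording such as 'TNE alone or added to unchanged prophylaxis', or, if the word means not combined with other non-drug therapies, say so in both places.
2. In section 2.10, prespecify baseline prophylaxis (yes/no) as a covariate in the primary model, in place of selection by a significant difference between arms. If the T1 value is modelled as a response, include the covariate's interaction with time. A main effect alone would leave the group-by-time contrast almost unchanged.
3. Optionally, report the T4 difference by prophylaxis status with 95% CIs, labelled exploratory, and draw any statement about TNE alone from the group without prophylaxis.

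The cost is a narrower headline claim and one covariate that eligibility screening already establishes. No extra patients or visits are needed. Nothing here bears on whether prophylaxis should be continued.

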## Figures and Tables

**Figure 1 mps-08-00022-f001:**
[figure not shown]
Timeline of the study design. QST, quantitative sensory testing; TNE-A, therapeutic neuroscience education arm; CON-A, control arm.

## Data Availability

No new data were created or analyzed in this study. Data sharing is not applicable to this article.
